## Procedure

The study procedure is illustrated in Fig. 3. The Standard Protocol Items: Recommendations for Interventional Trials (SPIRIT) figure shows the overview of the schedule of events (Fig. 4) (Additional file 1).

**Fig. 3 Fig3:**
[figure not shown]
Flow diagram for the study procedure

**Fig. 4 Fig4:**
[figure not shown]
Standard Protocol Items: Recommendations for Interventional Trials (SPIRIT) figure. Overview of the schedule of events

### Control group

Participants in the control group will receive routine medical care and participate in conventional physiotherapy and occupational therapy. Therapeutic programmes include lower limb strengthening exercises and traditional gait and balance training, upper limb functional training and activities of daily living practice. The rehabilitation programme will be provided for 5 days a week for 3 weeks, with each therapy session lasting for 1 h (total of 2 h).

### Intervention group

The intervention group will participate in a multisensory VR training programme for 5 days a week for 3 weeks. VR training is provided in addition to the routine programme. It consists of four components: gait training, limb coordination, gross motor function and fine motor function.

### Gait training

Gait training will be provided through the use of the GaitWatch system (JumHo, China). The system requires the use of seven transmitters strapped to the following points: the lumbar spine at the L4/L5 level, the mid-portion of the femur, the tibial tuberosity and the mid-foot region (on both legs). Figure 4 shows the GaitWatch system and the locations of the transmitters (Fig. 5a, b). GaitWatch provides a gait training programme with bespoke gaming activities, which include marching on the spot, lifting hips and knees to required position or walking in a virtual environment (Fig. 5c, d). Real-time feedback on the quality of movement will be provided to the participants. Figure 4 shows the GaitWatch system and the locations of the transmitters. Training sessions will last up to 20 min (excluding a 5-min break at the halfway mark). The system will produce a report on gait speed, maximum joint angle achieved, weight distribution and percentage of deviation from expected motion trajectory.

**Fig. 5 Fig5:**
[figure not shown]
GaitWatch system. **a** GaitWatch hardware. **b** Sensor position. **c** Real-time feedback displayed on the screen. **d** Walking tasks participants will be asked to complete

### Limb coordination and gross upper limb motor function

Limb coordination and gross motor function will be trained through use of the Microsoft Xbox 360 Kinect via the games Adventures and Fruit Ninja. Participants will be asked to perform tasks that are displayed on the screen at progressive difficulties. The Adventures game will encourage balance, mobility and stepping. Fruit Ninja will encourage shoulder flexion/extension and internal/external rotation and elbow flexion and extension. Body motion is captured by the associated motion-capturing device. A body-weight support harness will be provided to those who are not able to stand for a sufficient length of time (Fig. 6). The score achieved during the virtual game will be recorded to monitor progress. Each training programme will last for 10 min (total of 20 min training time in addition to a 5-min break), 5 days a week for 3 weeks.

**Fig. 6 Fig6:**
[figure not shown]
A body-weight support harness will be provided to those who are not able to stand for a sufficient length of time

### Fine motor function

The fine motor function of the upper limbs will be trained using the HandTutor™ glove (Fig. 7) with MediTutor software (Meditouch Ltd., [name], Israel). The device delivers training via bespoke games. The gloves capture the biomechanical motions of the fingers and wrists. Exercises can be tailored to train all fingers or isolated finger movements. Real-time feedback of quality of movement is displayed on the screen. The previously published exercise programme ‘Track’ [30] will be used as the exercise for this study. ‘Track’ is a programme where a ball moves along a track horizontally across the screen at varying heights. The movement of the ball is controlled by flexion and extension of the finger/s or wrist. The participant’s task is to keep the ball within the track by flexing and extending the finger/s or wrist, which changes the upward and downward gradients of the ball. The therapist can set the participant’s range of motion that will be exercised by changing the height of the track. The maximum range of movement represents the full vertical displacement of the ball on the screen. The measurement is a linear measurement and treats the fingers as a single joint. Fine motor training will last for 20 min (with a 5-min break every 6 min), 5 days a week for 3 weeks.

**Fig. 7 Fig7:**
[figure not shown]
HandTutor® glove for fine motor training

### Safety and adverse event reporting

The participants recruited into this study are patients with acute stroke with a likelihood of morbidity and mortality. Procedures are, therefore, in place to minimise adverse events. The risk relating to the intervention is minimised as patients who are medically unstable will be excluded from the study. Participants will not be asked to exercise beyond their physical ability. The exercise sessions will be delivered by trained physiotherapists/occupational therapists who will work closely with the inpatient clinical team, and they will have regular contact and access to the inpatient clinical team for any queries that may arise. The trial will adhere to the following safety reporting procedures:All serious adverse events (SAEs) related to the interventions will be recorded on an SAEs Event Report Form in accordance with local hospital procedure. A SAE is defined as an event that may harm the participant and may require medical or surgical intervention to prevent one of the following outcomes: death, a life-threatening situation, impairment of a body function, permanent damage to a body structure, and prolonged hospitalisationAll SAEs related to the interventions must be reported to the principle investigator within 24 h of learning of the eventSAEs that are related to the interventions will be reported to the special committee of the University Clinical Trial Unit and Research Ethics Committee within 15 days of the principle Investigator becoming aware of the event. Information that will be reported to relevant parties is: (1) appropriate identifying information for the research protocol, (2) a detailed description of the SAE and its outcome, (3) a description of any changes to the protocol or other corrective actions that have taken, or are proposed in response to the SAE

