The kinematic data of gait and upper limb motion will help to establish if functional improvement induced by early VR intervention is associated with changes of kinematic patterns. Buma [38] proposed that the desired outcome of stroke rehabilitation was to promote task completion in a manner that is close to normal movement pattern. Detailed kinematic information would enable the identification of potential compensation movement. Nonbiomechanical outcome measures had in the past misled clinicians to believe that a faster observed speed of reach forward movement execution may improve movement quality as appreciated by the smoothness [39]. However, recent biomechanical study has revealed that the faster execution speed observed in patients with stroke was related to trunk compensation movement [40]. A kinematic study is, therefore, essential to assess whether VR intervention is effective in promoting normal movement patterns as well as functional improvement.

In conclusion, this current research is set to provide information to demonstrate the clinical effectiveness of VR as part of an early intervention programme for patients with stroke.

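### The listed safety reporting covers only serious, intervention-related events; the article gives milder harms no recording route and plans no comparison of harm by arm

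*Protocol article*

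**What the plan says.** The protocol article, under Safety and adverse event reporting, acknowledges that patients with acute stroke are likely to experience morbidity and mortality, and says "Procedures are, therefore, in place to minimise adverse events". Two of the preventive measures are "The risk relating to the intervention is minimised as patients who are medically unstable will be excluded from the study" and "Participants will not be asked to exercise beyond their physical ability". The third is delivery by trained therapists who have access to the inpatient clinical team.

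The section then makes a commitment: "The trial will adhere to the following safety reporting procedures". Three procedures follow:

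- Recording: "All serious adverse events (SAEs) related to the interventions will be recorded on an SAEs Event Report Form in accordance with local hospital procedure".
- Reporting of related SAEs to the principal investigator within 24 h.
- Reporting of related SAEs to the trial-unit committee and the ethics committee within 15 days.

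The definition used is "A SAE is defined as an event that may harm the participant and may require medical or surgical intervention to prevent one of the following"; the list that comes next includes impairment of a body function and prolonged hospitalisation.

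The Outcome measures section and Table 1 contain no falls, pain, dizziness, fatigue or tolerability measure. The Data analysis section contains no safety analysis.

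**The concern.** The section heading promises adverse event reporting, but two filters must be passed before anything is written down: the event must be serious, and it must be judged related to the interventions. Many of the foreseeable harms of this programme fail the first filter.

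Participants are within a month of stroke, at Brunnstrom stage 2, and may need assistance to walk 10 m (Sample population). Some cannot stand long enough without a body-weight harness (Limb coordination and gross upper limb motor function). The VR arm adds marching and hip and knee lifting, and on the Kinect games "The Adventures game will encourage balance, mobility and stepping", with repeated shoulder and elbow movement.

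At stake is the balance of the final report. The Discussion says that "this current research is set to provide information to demonstrate the clinical effectiveness of VR as part of an early intervention programme". Those deciding whether to adopt the programme will want to set harm beside benefit, collected alike in both arms. The analysts cannot recover events that were never collected.

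**Working it through.** The document gives no safety figure to reproduce, so the check is mainly a reading of scope. A little arithmetic on exposure follows.

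**Step 1. Scope of each element of the safety section**

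| Element | Limited to serious events? | Limited to related events? | Produces a record? |
|---|---|---|---|
| Excluding medically unstable patients | No | No | Not of adverse events |
| No exercise beyond ability | No | No | No |
| Trained therapists with access to clinical team | No | No | No |
| SAE form | Yes | Yes | Yes |
| 24 h report to principal investigator | Yes | Yes | Yes |
| 15-day report to committees | Yes | Yes | Yes |

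The general measures reduce risk but count nothing. Every element that produces an adverse-event record carries both limits.

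**Step 2. Other possible recording routes**

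- Outcome measures and Table 1: function, kinematics, cognition, strength, muscle tone and disability; no harm measure.
- VR equipment: GaitWatch reports gait speed, joint angles, weight distribution and trajectory deviation; the Kinect games give a score. Neither is described as logging an event.
- Data management: biannual monitoring is planned, but monitors can review only what has been recorded.
- Data analysis: no table or test of harm.

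**Step 3. What falls inside and outside the SAE definition**

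The definition is loosely worded: the event may harm and may require intervention. A fall that may need treatment, or shoulder pain that may need treatment to prevent functional impairment, can meet it if judged related. A fall without injury, milder pain, transient dizziness or a session cut short for fatigue would ordinarily not meet it.

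**Step 4. Added exposure in the VR arm**

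Inputs: gait training up to 20 min, Kinect games 20 min and fine motor training 20 min (Intervention group subsections); 5 days a week for 3 weeks; 112 per group (Sample size); routine therapy 2 h in total, read here as daily (Control group).

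- VR time per day: 20 + 20 + 20 = up to 60 min.
- Treatment days: 5 × 3 = 15.
- Per participant: up to 15 × 1 h = 15 h on top of 15 × 2 h = 30 h of routine therapy.
- Whole arm: 112 × 15 = 1,680 participant-days, up to 1,680 h.

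These are ceilings. They assume full attendance and full-length gait sessions, while the sample size section allows for 10% missing.

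**Step 5. What a count would allow**

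If an event type were recorded and none occurred in 112 participants, the one-sided upper 95% limit would be 1 − 0.05^(1/112) = 2.6% per participant. With no recording route, no limit can be stated.

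**Step 6. Why the schedule matters**

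If the 2 h of routine therapy are two 1 h sessions (my reading of the Control group section), a per-session form gives 2 recording occasions a day in the control arm. The VR arm would have 3 if VR counts as one session (3/2 = 1.5 times as many) or 5 if each VR component counts separately (5/2 = 2.5 times as many). A fixed schedule removes this difference in ascertainment.

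**The case against.** The strongest reply is that this is an article, not the full protocol. It refers to report forms, a purpose-built data system, a schedule of events and a supplementary file, none of which is shown. Non-serious events may be captured there, and silence in a condensed article is not evidence that they go unrecorded. This stands as a limit: the finding concerns what the article sets out, not what is collected in practice. It does not remove the finding. The article does not defer safety reporting elsewhere. It gives the form, the definition, two deadlines, the recipients and the report contents, and commits the trial to them, so the narrow scope is stated.

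A reader might also infer more than the text supports:

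- **That all safety procedures concern serious events only.** They do not. The preventive measures apply to any adverse event; only the recording and reporting procedures are restricted.
- **That falls and pain would never be counted.** The definition is broad enough to take in an injurious fall or pain needing treatment, if judged related. The milder remainder is what lacks a route.
- **That the trial fails at a tolerability aim.** It states none. The Hypotheses and Discussion promise effectiveness. The remark on home use is background, and all interventions are delivered in the hospital department.
- **That a specific number of events will be lost.** An assumed rate of 0.5% to 2% of the 1,680 participant-days would give 8.4 to 33.6 events, but the rate has no basis in the document and some of those events could qualify as SAEs. The conclusion does not use this estimate.

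**Conclusion.** The point holds in a limited form. As written, adverse-event recording is confined to serious events judged related to the interventions, and the article describes neither recording of non-serious events nor a safety summary by arm. Non-injurious falls, milder pain, dizziness and shortened sessions therefore have no stated route into the data, and the text gives no basis for comparing them between arms.

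The gap concerns the completeness of the evidence on harm. It does not affect the gait-speed analysis or its power. Its size in events cannot be stated; the document supports only the exposure, at most 15 additional hours per VR participant. The conclusion assumes that the three listed procedures are the whole of adverse-event recording, as the article's wording suggests. If unshown forms already collect non-serious events alike in both arms, what remains is to say so in the article and add the table.

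**What to change.** Extend the safety section to record adverse events regardless of seriousness: falls and near-falls, new or worse pain, dizziness or nausea, and sessions shortened or stopped, with the reason. Keep the SAE reporting deadlines as a separate layer.

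Use the same form on the same fixed schedule in both arms, for example once per treatment day or once per week for the 3 weeks, and at each outcome visit. Do not tie the form to each session, because VR is given on top of routine therapy and the VR arm would be observed more often.

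Add to Data analysis a descriptive safety outcome: the number and percentage of participants with each event, by arm. For shortened sessions, show routine and VR sessions separately, since only one arm has VR sessions to shorten.

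Cost: a short form completed by therapists and assessors already present, and one table. With the four post-baseline visits, daily recording gives 15 + 4 = 19 forms per participant (19 × 224 = 4,256 in all); weekly recording gives 3 + 4 = 7 (7 × 224 = 1,568). More events will be reported in both arms. Recruitment has run since May 2015, so if the form is new, the report should give its start date and restrict the table to participants followed under it.

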**Methods:**

Two hundred and twenty-four acute stroke patients will be recruited from a single centre over a period of 6 years. Participants will be randomly assigned to either conventional therapy or conventional therapy with VR training. Outcomes will be recorded at baseline, post intervention and at 3, 6 and 12 months post intervention. Primary outcome measure is gait speed. Secondary outcome measures include kinematic data of upper and lower limb motion, muscle tone, Action Research Arm Test and Short Orientation Memory Concentration Test.

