## Methods

### Study design

This study is a single-blind randomised controlled trial (RCT) to compare the differences between two parallel groups.

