### Study setting

This is a single-centre study which will be conducted by the Rehabilitation Department of the Sun Yat-sen University, China. Participants will be recruited from the inpatient ward. All interventions will be delivered within the Hospital Rehabilitation Department by hospital staff.

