## Data analysis

Descriptive statistics will be used to describe the demographic data of each sample group. The normality of each parameter will be checked by histogram and the Kolmogorov-Smirnov test.

Chi-squared tests will be used to assess sample characteristics of gender and types of cerebral infarction.

The pre- and post-intervention differences in gait speed within individuals and between groups will be assessed by paired-samples *t* tests (two-tailed) and one-way analysis of variance (ANOVA), respectively. The comparison of 3-month, 6-month and 1-year follow-ups will be assessed by repeated-measures ANOVA.

A broadly similar approach will be used to analyse the secondary outcome measures of muscle tone, other kinematic parameters of gait, reach forward motion and reach forward and grasp motion. The kinematic parameters of the paretic side will be compared with the nonparetic side at all recording points using paired-samples *t* tests.

The Mann-Whitney *U* test will be used to test the between-group differences for the ordinal data obtained from the functional outcome measures and WHODAS 2.0.

The differences between the two groups during the follow-up phase will be assessed by the Kaplan-Meier test.

There are no planned interim analyses or stopping rules, as the power calculation has accounted for loss to follow-up. All analyses will initially be performed on an intention-to-treat basis.

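### SAE recording, not only expedited reporting, is limited to intervention-related events, and the SAE definition omits new admission, so unrelated deaths, recurrent strokes and readmissions have no stated route into the trial data

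*Protocol article*

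**What the plan says.** The rule is in the protocol article under Safety and adverse event reporting. An SAE is "an event that may harm the participant and may require medical or surgical intervention to prevent one of the following outcomes: death", and the list goes on to a life-threatening situation, impaired body function, permanent structural damage and prolonged hospital stay.

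Three steps follow, each with the same qualifier:

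- Recording: "All serious adverse events (SAEs) related to the interventions will be recorded on an SAEs Event Report Form", in line with local hospital procedure.
- Related SAEs go to the principal investigator within 24 h of the event becoming known.
- Related SAEs go to the Clinical Trial Unit's special committee and the ethics committee within 15 days.

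The same section describes participants as "patients with acute stroke with a likelihood of morbidity and mortality". Under Study setting, "Participants will be recruited from the inpatient ward". The abstract says: "Outcomes will be recorded at baseline, post intervention and at 3, 6 and 12 months post intervention". Data management has the special committee monitor study conduct and data collection twice a year. Data analysis plans no interim analyses and no stopping rules.

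**The concern.** Restricting expedited reporting to related events is ordinary practice. Restricting recording is different, because a judgement about cause then decides which events exist in the data at all. In a randomised trial, the safeguard against mistaken attribution is to count all serious events in each arm and let randomisation show any difference. A filter applied before recording removes that safeguard.

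The issue matters here for three reasons. Patients early after stroke can be expected to have serious events whatever the treatment. One arm receives extra marching, stepping and balance work on top of the routine programme. And a death or recurrent stroke would also explain a missing or sharply reduced gait speed, the primary outcome. The sample size section allows for 10% missing, which is about 22 of 224 participants (0.10 × 224 = 22.4). A count of all serious events by arm would help to show whether such losses are balanced.

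**Working it through.** No stated figure needs to be reproduced, and the article gives no SAE, death or readmission rate, so the check is a close reading.

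**1. Where the filter sits.** The relatedness qualifier is attached to all three steps: the form, the 24 h report and the 15-day report. An unrelated SAE therefore fails at the first step.

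**2. Whether another route exists.**

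- Outcome measures, including Table 1, contain gait speed, function, cognition, balance, strength, muscle tone, disability and kinematics. None is death, readmission, recurrent stroke or falls.
- Data management describes data entry and monitoring but no wider event log.
- Data analysis contains one time-to-event method: "The differences between the two groups during the follow-up phase will be assessed by the Kaplan-Meier test". No event is defined for it, so it does not imply that deaths or SAEs are collected.

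**3. Events taken through the rule.**

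- A serious fall in a VR session, judged related: meets the definition and is recorded.
- A related event that proves fatal: very probably recorded, since an event that may harm and may require intervention to prevent death covers it in sense, though there is no results-in limb.
- A serious fall in a control participant's gait or balance session: can be recorded, because the text says interventions in the plural and controls also receive therapy.
- A recurrent stroke between the 3- and 6-month visits, judged unrelated: probably meets the definition, but has no stated recording route.
- A death between the 6- and 12-month visits, judged unrelated: no stated recording route.
- A readmission after discharge: not listed as such. It must first be fitted under another item on the list and must then also be judged related.

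**4. How much of the observation period this touches.** Treatment lasts 3 weeks and follow-up runs for 12 months, or about 52 weeks, afterwards. The treatment period is 3/(3 + 52) = 3/55, about 5% of the total. In the remaining 95% or so no trial session is taking place, and serious events are less likely to be attributed to the interventions. Participants start as inpatients, so after discharge a serious event would usually appear as a new admission, the item missing from the list. The 5% describes time only. It is not an estimate of the share of events affected.

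**5. Comparability between arms.** Study design says: "This study is a single-blind randomised controlled trial (RCT) to compare the differences between two parallel groups". It does not say who is blinded, but therapists delivering VR must know the allocation. The safety section does not say who judges relatedness. If treating staff do, or supply the account on which it is judged, similar events may be attributed differently in the two arms. The direction cannot be derived from the text.

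**The case against.** The strongest reply is that this is a condensed article. It nowhere says that unrelated events go unrecorded, and the local hospital procedure it cites may capture more. That holds up to a point. A reader might infer that every unrelated SAE is certainly lost, and the article does not establish this: the word only is absent and the local procedure is not shown. But the article does not merely leave the scope of recording to another document. It states the scope, repeats it at each step, and invokes the local procedure for how related SAEs are recorded, not for which events qualify.

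Two other strong readings are tempting and should not be adopted:

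- That relatedness cannot arise in the control arm. The text refers to interventions in the plural, and controls receive strengthening, gait and balance training, so a control participant can have a related event. The supportable point is that attribution may differ between arms.
- That deaths fall outside the definition. Read very literally there is no limb for events that result in death, but the wording is loose and the 15-day report must describe the SAE's outcome. For related deaths this is a defect of wording.

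It is also fair to say that serious falls during training sessions are the events most likely to be called related and so captured, and that the hypotheses and outcomes contain no safety endpoint. No stated efficacy comparison is therefore miscalculated because of this rule.

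**Conclusion.** The point holds at moderate severity. The recording rule, as written, admits only related SAEs, and the definition names prolonged but not new hospitalisation. Deaths, recurrent strokes and readmissions judged unrelated have no stated route into the trial data for up to 224 participants over 12 months. On the reports described, the committee could not compare total serious harm between arms, and with no interim analyses planned its twice-yearly review is the only continuing oversight stated.

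No number of missed events can be given, and none should be implied. An upper confidence bound calculated from a zero count of recorded events would describe related events alone and would not measure this defect.

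The conclusion assumes that staff follow the text as printed and that no undisclosed form or local procedure collects all SAEs. If one does, the remedy reduces to correcting the article's wording and the definition. The remark on attribution assumes that treating staff influence the relatedness judgement, which the article neither states nor excludes.

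**What to change.** Amend the safety section in four respects:

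1. Define an SAE to include any event that results in one of the listed outcomes, and add new hospitalisation beside prolonged stay.
2. Record all SAEs in both arms from randomisation to 12 months post intervention regardless of relatedness, with relatedness as a separate field on the form.
3. Keep the 24 h and 15-day reports for related SAEs as they stand.
4. Give the committee total SAEs by arm at each twice-yearly review.

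The cost is a protocol amendment, a revised report form and modest extra recording at the post-intervention, 3-, 6- and 12-month visits, which already take place. Recruitment has been open since May 2015, so events in participants already enrolled should be collected retrospectively as far as records allow. These may be hard to recover reliably, which argues for making the change soon.
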